### Participant recruitment

3.5

Participants for this study will be recruited from the broader Sydney region of Australia. Recruitment efforts will include general announcements on the university research study website, postings on noticeboards, sign-up sheets, and engagement by research team members who have no prior relationship with potential participants to minimise any risk of coercion. Within the University community, recruitment will be further facilitated through e-bulletins such as “Yamma” and “Volunteer for Research Studies.” Additionally, the study will be advertised on social media platforms, including Facebook and Instagram, with all promotional materials prominently featuring the research team's contact information. Interested individuals will be able to reach out directly to the research team for more details. Participation in the study will be entirely voluntary, and all outreach materials will explicitly highlight this to ensure informed and voluntary engagement.

### Pre-testing familiarization session

3.6

To minimise learning effects that could otherwise inflate post-intervention performance outcomes, all participants will complete a dedicated familiarisation session prior to baseline testing. This session is particularly important given that participants are inexperienced with structured RT and the pneumatic resistance equipment used in this study. The session will include guided, hands-on instruction covering all outcome measures (i.e., 1RM dynamic strength, MVC, muscle power, and muscular endurance). Participants will be instructed on proper lifting techniques, breathing control, equipment handling, and movement cadence specific to each test (e.g., 2-1-2 tempo for dynamic lifts, 5-s holds for isometric efforts). They will also be introduced to equipment feedback systems, including real-time force and power displays, to ensure familiarity with test procedures. The goal of this session is to ensure that participants are confident, consistent, and technically proficient during all baseline assessments. This approach enhances the accuracy, reliability, and reproducibility of performance data across timepoints.

### Data collection

3.7

An identification code will be used to identify participants' data. The study's principal investigator will create the identification code, and these details will not be shared with the rest of the research team. This approach ensures the confidentiality and anonymity of participants' data, protecting their privacy in accordance with ethical research standards. Only the study's chief investigator will have access to the code to link participant identities if necessary for follow-up or data verification. The research staff will enter the data gathered into REDCap Digital, a secure web application hosted by the University of Sydney that builds and manages databases [12].

## Outcome measures

4

### Dynamic strength (1RM)

4.1

Dynamic muscular strength will be assessed using a 1RM test for both the chest press and leg press (Keiser Sports Health Equipment, Inc., Fresno, CA, USA). In accordance with National Strength and Conditioning Association (NSCA) and American College of Sports Medicine (ACSM) protocols, participants will first complete a general warm-up followed by a specific warm-up consisting of multiple submaximal repetitions at a light-to-moderate intensity (corresponding to a rating of perceived exertion [RPE] of 4–6 on the Borg CR10 scale) to reduce the risk of injury and ensure neuromuscular readiness. Following the warm-up, participants will perform single repetitions with progressively increased loads. A successful lift will be defined as the ability to complete the full ROM with proper technique and control. Rest intervals of 2–3 ​min will be provided between attempts to allow adequate recovery, as recommended by NSCA guidelines. If a participant reports an RPE ≥9 (on the 0–10 scale), the rest period may be extended up to 4 ​min. The test will conclude when the participant is unable to complete the lift for two consecutive attempts at a given load. The highest load successfully lifted will be recorded as the 1RM. All 1RM testing will be conducted under strict safety protocols, including proper machine setup and clear verbal instructions. Standardised verbal encouragement will be provided throughout the testing to promote maximal effort.

### Isometric strength

4.2

Maximal isometric strength will be evaluated for both the chest press and leg press using MVCs at the same joint angles applied during the ISO-RT intervention: one-third (just before lockout), two-thirds (mid-range), and the end of the eccentric phase. Testing will be conducted using a custom-built isometric rig equipped with a calibrated force transducer, with real-time force output displayed on a monitor (as described in section 3.3). At each angle, participants will perform three maximal 5-s contractions, with a 2-min rest interval between attempts to ensure adequate recovery and minimise fatigue. If a participant reports an RPE of 9 or higher on the Borg CR10 scale, the rest period may be extended to 3 ​min. The highest recorded force at each angle will be used as the participant's MVC. Joint angles will be measured using a goniometer during the familiarisation session and replicated consistently across all testing sessions. Standardised verbal encouragement will be provided during each contraction to promote maximal effort.

### Muscle power

4.3

Muscle power will be assessed using Keiser pneumatic resistance equipment with K400 electronics. Participants will perform a single explosive contraction at incremental loads ranging from 20 ​% to 80 ​% of their most recent 1RM (in 10 ​% increments) for the chest press and leg press. A 60-s rest will be provided between efforts, with one practice trial at 20 ​% 1RM before progressing to higher loads. Peak power outputs will be recorded at each load.

### Dynamic muscular endurance

4.4

Dynamic muscular endurance for the chest press and leg press will be evaluated using Keiser pneumatic resistance equipment, set at a standardised load of 60 ​% 1RM. Participants will perform as many repetitions as possible with proper form, adhering to the 2-1-2 ​s cadence (2-s concentric, 1-s pause, 2-s eccentric) used during training sessions. The test will be terminated when the participant is unable to complete a repetition with proper form or maintain the prescribed cadence for two consecutive repetitions. Recorded metrics will include the total number of repetitions, total work performed, as well as the velocity and power generated during the first and last repetitions.

### Isometric muscular endurance

4.5

Isometric muscular endurance for the chest and leg press will be assessed using Keiser pneumatic RT equipment. Participants will perform intermittent isometric contractions set at 80 ​% of their predetermined MVC. Equipment adjustments will ensure participants’ joints are positioned at the midpoint of the concentric phase. The protocol comprises repeated cycles of a 5-s isometric contraction at 80 ​% MVC followed by a 5-s rest interval. The ISOTrainer live visual feedback module will enable participants to maintain accurate and consistent contraction intensity throughout the test. The test will terminate when participant-generated force falls below 50 ​% MVC during two consecutive repetitions. Recorded metrics will include the total number of successful contractions (repetitions) and the total time to exhaustion (in seconds).

### Body composition

4.6

Body composition (i.e., whole-body and appendicular muscle mass) will be measured in whole-body scan mode at baseline and post-intervention using Dual-energy X-ray Absorptiometry (DEXA) (Lunar Prodigy, GE Medical Systems, Madison, WI) [13]. All scans will be conducted under standard conditions by a licensed co-investigator. Participants will be instructed to adhere to pre-scan guidelines, including a minimum 12-h fast from solid food, a 6-h fast from liquids, and refraining from exercise for at least 24 ​h. The in-built enCORE analysis software (version 13.60.033; GE Healthcare) will be used to calculate total lean mass, fat mass, and regional composition (e.g., appendicular lean mass for upper and lower limbs). To minimise variability and enhance the accuracy of measurements, participants will be instructed to follow standardised pre-scan procedures, including fasting from solid food for at least 12 ​h, refraining from liquid intake for 6 ​h, avoiding vigorous physical activity for at least 24 ​h, and voiding their bladder and bowels within 60 ​min prior to the scan. Adherence to these protocols will be confirmed verbally by study staff prior to each scanning session.

### Sleep quality

4.7

Sleep quality will be assessed using the Single-Item Sleep Quality Scale (SQS), a validated tool designed to capture overall subjective sleep experience over the past 7 days [14]. Participants will rate their sleep quality on an 11-point numerical scale ranging from 0 (“terrible”) to 10 (“excellent”), considering various aspects such as sleep duration, ease of falling asleep, night-time awakenings, early morning awakenings, and perceived restfulness upon waking. This measure provides a simple yet reliable index of perceived sleep quality, which may influence recovery and training responsiveness [14].

### Muscle soreness

4.8

Perceived muscle soreness will be measured using a 100-mm Visual Analogue Scale (VAS), a widely accepted method for quantifying delayed onset muscle soreness (DOMS). Participants will be asked to indicate the intensity of soreness they feel in the chest and leg muscles, respectively, by marking a point on the horizontal line where 0 ​mm represents “no pain” and 100 ​mm represents “severe, intolerable pain.” The VAS will be administered at 24- and 48-h post-training following each exercise session throughout the intervention period. This approach allows for the tracking of exercise-induced muscle soreness and its potential modulation across different RT modalities [15].

## Statistical analysis

5

### Sample size

5.1

As this is a pilot study with an exploratory focus, no formal a priori power calculation has been conducted, as the primary objective is not to test hypotheses but to estimate effect sizes, assess outcome variability, and evaluate the feasibility of the intervention protocol. Moreover, due to the limited availability of previous studies employing comparable designs (i.e., directly comparing isometric and dynamic RT on strength and body composition), there is insufficient data to support a reliable power analysis at this stage. Based on methodological recommendations for pilot trials, a total sample size of 20 participants (10 per group) is considered appropriate for this phase of investigation. This is consistent with established guidance suggesting that 10–12 participants per group are sufficient to estimate key design parameters such as effect size variability, adherence, and procedural feasibility in small-scale studies [16,17]. Although the sample is not powered to detect statistically significant between-group differences, post hoc sensitivity analysis indicates that, with an alpha of 0.05 and 80 ​% power, the study would be able to detect very large effect sizes (Cohen's d ​≥ ​1.2). While detecting effects of this magnitude would suggest strong intervention potential, the primary aim of this study is to generate preliminary data to inform the design and powering of an adequately powered trial in the future.

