### Data analysis plan

5.2

The effects of ISO-RT vs. DYN-RT on primary outcomes (isometric and dynamic muscular strength and power) and secondary outcomes (muscle hypertrophy, muscular endurance, and muscle oxygenation) will be analysed using a two-way repeated measures ANOVA, with time (pre- and post-intervention) as the within-subject factor and group (ISO-RT vs. DYN-RT) as the between-subject factor. Where significant main effects or interactions are observed, Bonferroni-adjusted post hoc tests will be used to determine pairwise differences. To compare between-group percentage changes in outcome variables (e.g., strength, power, isometric and dynamic muscular endurance, hypertrophy) a one-way ANOVA will be conducted, followed by Bonferroni correction for multiple comparisons. All analyses will be conducted using SPSS software (Version 29.0; IBM Corp., Armonk, NY, USA), with statistical significance set at p ​< ​0.05.

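### Section 5.1's detectable effect of d ≥ 1.2 does not follow from 10 per group: a two-sided comparison needs d of about 1.32 (minor correction)

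*Protocol article*

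**What the plan says.** Section 5.1 (Sample size) of the protocol article says that "no formal a priori power calculation has been conducted" and rests the sample size on guidance for pilot trials: "a total sample size of 20 participants (10 per group) is considered appropriate for this phase of investigation". It then adds a sensitivity statement. The sentence opens with "Although the sample is not powered to detect statistically significant between-group differences" and goes on to say that, at alpha 0.05 and 80% power, "the study would be able to detect very large effect sizes", with Cohen's d of at least 1.2 in brackets. It does not name the test, its sidedness, the SD that scales d, or a pre-post correlation.

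Section 5.2 (Data analysis plan) gives the tests. Primary and secondary outcomes "will be analysed using a two-way repeated measures ANOVA, with time (pre- and post-intervention) as the within-subject factor" and group as the between-subject factor. For percentage changes between the groups, "a one-way ANOVA will be conducted, followed by Bonferroni correction for multiple comparisons". Significance is set at p < 0.05.

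**The concern.** A detectable effect is fixed by the group size, alpha, power and the test. Section 5.1 prints the first three and makes the contrast a between-group one; section 5.2 supplies the test. The printed d should therefore be reproducible, and 1.2 looked too small for 10 per group.

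This is the only operating characteristic the article gives. If it is optimistic, readers are told that a true effect of d = 1.2 would be missed in 20% of such trials, when under the plain reading it would be missed in about 28%. The section also treats effects of this size as a sign of strong intervention potential, so the number has some interpretive use.

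**Working it through.** **Inputs**
- n = 10 per group, alpha 0.05, power 80%, between-group contrast: section 5.1.
- Two-sided: inferred from section 5.2. An ANOVA F test has no direction. With two groups, the one-way ANOVA on percentage change is the two-sided two-sample t test (F = t²). The time-by-group interaction in a two-group, two-time ANOVA is likewise the t test on the change score. The Key points also leave the direction of the difference open.

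**Formula.** With n per group, df = 2n − 2 and noncentrality = d·√(n/2). Power is the probability that a noncentral t variable with that df and noncentrality falls outside ±t(0.975, df).

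**Attempt to reproduce 1.2.** For n = 10, df = 18, the critical value is 2.101 and noncentrality = d·√5 = 2.236·d.
- At d = 1.2: noncentrality = 2.683, power = 71.8%.
- Solving for 80% power: d = 1.325 (1.3249), noncentrality = 2.963.

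The normal approximation does not give 1.2 either: d = (1.960 + 0.842)·√(2/10) = 2.802 × 0.447 = 1.253, with 76.5% power at d = 1.2.

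**What would give about 1.2**

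| Setting | d at 80% power | Power at d = 1.2 |
|---|---|---|
| 10 per group, two-sided t | 1.325 | 71.8% |
| 11 per group, two-sided t | 1.256 | 76.3% |
| 12 per group, two-sided t | 1.197 | 80.2% |
| 10 per group, one-sided t | 1.156 | 82.5% |

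**Raw-SD scaling.** If d is expressed in SDs of the outcome itself and the interaction is tested, the SD of the change is the raw SD times √(2(1 − ρ)), where ρ is the pre-post correlation (equal SDs at both times assumed). The detectable d becomes 1.325·√(2(1 − ρ)). Setting this to 1.2 gives 2(1 − ρ) = (1.2/1.325)² = 0.820, so ρ = 0.59. The article gives no ρ, so this range is an assumption:

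| Assumed ρ | Detectable d (raw SD) | Power at d = 1.2 |
|---|---|---|
| 0 | 1.87 | 43.5% |
| 0.4 | 1.45 | 64.0% |
| 0.5 | 1.32 | 71.8% |
| 0.6 | 1.19 | 81.0% |
| 0.7 | 1.03 | 90.6% |

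**The case against.** The strongest defence is that section 5.1 names neither a test nor an SD scale, while the main analysis is a repeated measures model. On the raw-SD scale, any pre-post correlation of about 0.59 or more makes 1.2 correct or conservative. That stands as a possibility, so it cannot be said that 1.2 is wrong under every reading. But the section states no correlation, and it says that the available data do not support a reliable power analysis. A reader given only n, alpha, power and Cohen's d will take the standard two-group calculation.

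A one-sided test gives 1.156, which rounds to 1.2, but it conflicts with the non-directional F tests of section 5.2. The result for 12 per group matches the top of the 10–12 range that section 5.1 cites, but the trial enrols 10. The origin of 1.2 cannot be known from the article.

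The second defence concerns importance, and it stands. The sentence itself disclaims power for group differences, the section says that testing hypotheses is not the primary objective, and n = 20 comes from pilot guidance. Both 1.2 and 1.32 carry the same message: only very large effects are detectable. A reader might infer that the error undermines the sample size, or that a null result will be over-read. The documents do not support either inference, given those disclaimers.

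A reader might also want to add losses to follow-up or a Bonferroni correction across all strength variables. Neither belongs to this point. A condensed article may leave an attrition allowance to the full protocol, and section 5.2 does not specify a correction across a defined set of strength variables.

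**Conclusion.** The printed sensitivity does not follow from the inputs beside it. For a two-sided 5% comparison of 10 versus 10 on one outcome, the detectable difference at 80% power is d ≈ 1.32 rather than 1.2. Power at d = 1.2 is about 72%, some 8 percentage points short.

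This rests on three assumptions: two-sided testing, which the planned ANOVA implies; d in SD units of the variable analysed; and all 10 per group contributing data. If d was meant in raw-SD units, the figure depends on a correlation that the article does not give.

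This is a minor correction. It changes no sample size, endpoint, analysis or decision rule.

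**What to change.** Keep n = 20. Replace the sensitivity sentence in section 5.1 with:

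> With 10 per group completing, two-sided alpha 0.05 and 80% power, the detectable standardised between-group difference (in SD units of the analysed variable, e.g. the change score) for a single outcome is d ≈ 1.32; power at d = 1.2 is about 72%.

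If 1.2 was intended in raw-SD units under the repeated measures model, keep it, but state the test and the assumed pre-post correlation that produce it.

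The cost is one sentence and a slightly less favourable figure. The design and the analysis stay as they are.

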### Data analysis plan

5.2

The effects of ISO-RT vs. DYN-RT on primary outcomes (isometric and dynamic muscular strength and power) and secondary outcomes (muscle hypertrophy, muscular endurance, and muscle oxygenation) will be analysed using a two-way repeated measures ANOVA, with time (pre- and post-intervention) as the within-subject factor and group (ISO-RT vs. DYN-RT) as the between-subject factor. Where significant main effects or interactions are observed, Bonferroni-adjusted post hoc tests will be used to determine pairwise differences. To compare between-group percentage changes in outcome variables (e.g., strength, power, isometric and dynamic muscular endurance, hypertrophy) a one-way ANOVA will be conducted, followed by Bonferroni correction for multiple comparisons. All analyses will be conducted using SPSS software (Version 29.0; IBM Corp., Armonk, NY, USA), with statistical significance set at p ​< ​0.05.

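### Most pre/post outcomes are tested twice on different scales with no stated precedence, and main effects open post hoc tests; one baseline-adjusted ANCOVA per outcome would give a single estimate of the randomised contrast.

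*Protocol article*

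**What the plan says.** Section 5.2 (Data analysis plan) of the protocol article sets out three steps, all at p < 0.05.

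- First, a group-by-time repeated-measures ANOVA is applied to the primary and secondary outcomes named there.
- Second, follow-up testing is opened by any significant term of that model: "Where significant main effects or interactions are observed, Bonferroni-adjusted post hoc tests will be used to determine pairwise differences".
- Third, the arms are compared again on each participant's percentage change, using a one-way ANOVA with a Bonferroni correction. Strength, power, both kinds of endurance and hypertrophy are given as examples.

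The section does not say which of the two ANOVAs gives the trial's answer when they differ. Section 5.1 (Sample size) describes the purpose differently: "the primary objective is not to test hypotheses but to estimate effect sizes, assess outcome variability, and evaluate the feasibility".

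**The concern.** With two groups and two time points, the randomised question sits in one term, the group-by-time interaction. The other two terms do not answer it.

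- The group main effect averages the post value with a baseline taken before any training, so a true post-training difference appears at half its size.
- The time main effect asks whether participants improved. Section 3.4 admits people with no structured resistance training in the past three months, and both arms then train for six weeks. A time effect is therefore expected whether or not the arms differ.

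Letting either main effect open post hoc testing means follow-up tests will often run when there is no evidence of a difference between arms. If they are within-arm pre-post comparisons, they invite the conclusion that one programme works and the other does not, because only one arm reached significance.

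The percentage-change ANOVA then asks the between-arm question again on another scale, with each participant's baseline in the denominator. At stake is which estimate goes forward to the larger trial that this pilot is meant to inform.

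**Working it through.** **Inputs.** From the article: 20 participants, 10 per group, alpha 0.05 (sections 5.1 and 5.2), and one baseline and one post-intervention assessment. Not given, so assumed: baseline-post correlation r from 0.5 to 0.95, SD 20-30% of the baseline mean, and a common training gain of 0.5-1.0 SD.

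**The plan's own figure.** Section 5.1 gives a detectable Cohen's d of 1.2 or more at 80% power. The two-sided normal approximation gives (1.960 + 0.842) × √(2/10) = 1.25. A two-sided t-test on 18 df gives 1.32, and a one-sided t-test gives 1.16. The figure is mildly optimistic if two-sided. That is a separate, minor matter, and nothing below depends on it.

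**1. What the interaction tests.** With two time points, the interaction F equals the square of the t statistic comparing change scores between groups on 18 df. The expected group main effect is (0 + δ)/2 = δ/2 for a true post-training difference δ.

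**2. How often main effects open the post hoc tests.** This was simulated with 20,000 trials per setting, no group difference and a gain of 0.5-1.0 SD in both arms. Post hoc tests were opened in 60-100% of trials, almost always by time. If they are within-arm pre-post tests, exactly one arm was significant in 0-49% of trials, depending on r and the gain.

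**3. Two tests of one contrast, no true difference.** At least one test was significant in 5.5-7.6% of trials. Two independent tests would give 1 − 0.95² = 9.75%; these two are strongly correlated.

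**4. Two tests, true additive difference of 0.6 SD (SD 30% of the mean).**

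| r | Interaction power | Percentage-change power | ANCOVA power | Two ANOVAs disagree |
|---|---|---|---|---|
| 0.5 | 25% | 15% | 30% | 12% |
| 0.7 | 37% | 23% | 40% | 17% |
| 0.8 | 52% | 32% | 54% | 23% |
| 0.9 | 81% | 51% | 81% | 32% |

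In a second setting the baseline mean is 15, SD 4, r = 0.8, with a 1-SD additive effect and a common gain of 0.75 SD. Power there is about 65% for percentage change, 91% for the interaction and 92% for ANCOVA; a repeat simulation agreed to within about a point. The common gain matters. At r = 0.5, percentage change has about 35% power with it and about 43% without it.

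**5. ANCOVA against the change score with 10 per group.** In units of σ² × 2/10, the change-score variance is 2(1 − r). The ANCOVA variance is (1 − r²) × (1 + 1/16), where the last factor is the cost of estimating the slope with N = 20. The ratio is therefore (1 + r)/2 × 17/16.

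| r | Ratio | Detectable d, change | Detectable d, ANCOVA |
|---|---|---|---|
| 0.5 | 0.75 × 1.0625 = 0.80 | 1.32 | 1.19 |
| 0.7 | 0.85 × 1.0625 = 0.90 | 1.03 | 0.98 |
| 0.8 | 0.90 × 1.0625 = 0.96 | 0.84 | 0.82 |
| 0.9 | 0.95 × 1.0625 = 1.01 | 0.59 | 0.60 |
| 0.95 | 0.975 × 1.0625 = 1.04 | 0.42 | 0.43 |

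Break-even is r = 2 × 16/17 − 1 = 0.88. Simulated variance ratios agreed with the formula.

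**The case against.** The strongest reply is that the interaction is already a valid, unbiased test of the randomised contrast, so replacing it with ANCOVA is an efficiency preference in a small pilot that disclaims hypothesis testing. The premise is correct: the interaction test is sound. The reply does not cover the second test or the main-effect trigger, and an estimation aim argues for one named estimate rather than two tests at p < 0.05.

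It can also be said that section 5.2 names the repeated-measures ANOVA first, and that a separate analysis plan may rank the two. That may be so, and a missing ranking alone would be a weak point. What stands is that the published text prescribes both tests and the trigger.

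A reader might infer several stronger claims that the article does not support:

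- **That ANCOVA is always more precise, by 5-25%.** Those gains are the large-sample ratio (1 + r)/2. At N = 20 they shrink and reverse above r of about 0.88. The article gives no r. Wide between-person spread in a mixed-sex sample would push r up, towards the range where the gain disappears.
- **That the false-positive rate nearly doubles.** It rises to about 6-8%.
- **That within-arm tests are prescribed.** The text says only pairwise differences, and a follow-up to a time effect could equally be the pooled pre-post contrast, which adds nothing new.
- **That every outcome is tested twice.** Muscle oxygenation is not among the percentage-change examples, and section 5.2 names no test for sleep quality or soreness.
- **That percentage change always loses power.** If effects are purely proportional it loses none, and ANCOVA on log values does nearly as well.

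**Conclusion.** The point holds for strength, power, endurance and hypertrophy. The plan tests one contrast twice on different scales without saying which governs, and it lets terms that do not estimate that contrast open further testing. The main harms are disagreement between the two tests (roughly 10-30% of trials at r up to about 0.8, under additive effects of 0.6-1 SD) and a trigger that operates in most trials even when the arms do not differ. The inflation of the false-positive rate is minor. The disagreement and power figures rest on an assumed additive effect, SD, training gain and r, none of which the article supplies. The duplicate test and the trigger are read directly from the text and need no assumption. This is an inexpensive improvement that should be made; it does not make the planned interaction test invalid.

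**What to change.** In section 5.2, for each pre/post outcome:

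- Name one analysis: ANCOVA of the post value on group and baseline value, reporting the adjusted difference with its 95% CI. Where a relative effect is wanted, fit it on log values and back-transform to a ratio.
- Delete the one-way ANOVA on percentage change. Its pairwise Bonferroni step goes with it, since two groups leave only one comparison.
- Delete the post hoc tests opened by main effects, and show within-arm changes descriptively.

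The cost is a change of wording and one degree of freedom, with the same data and software. In precision it costs at most about 4% in variance for correlations up to 0.95, and it gains about 20% at a correlation of 0.5.
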